#### Cognitive and sociodemographic background

2.5.7

A demographics questionnaire will be used to assess sex, gender, sexuality, preferred pronouns, height, and weight. The Parent and Child Mini-Forms will be used to assess data regarding FS (e.g., data of FS onset and diagnosis. presence of premonitory symptoms) at baseline. The Parent and Child Mini-Forms will also be used to assess other baseline characteristics (e.g., school status, medication use, hospital visits), and this data will be collected again via the Child and Parent Follow-Up Forms. The COVID-19 FND Questionnaire will be used to assess participants’ COVID-19 history.

The Shipley Institute of Living Scale (Shipley IQ) will be used to assess crystallized and fluid cognitive abilities. The Shipley IQ has demonstrated good reliability and validity across clinical and non-clinical samples (57). The Healthcare-Related Stigma Questionnaire will be used to assess FS-related experiences with healthcare providers. The Childhood Trauma Questionnaire (CTQ) will be used to assess history of physical, sexual, and emotional abuse, and physical and emotional neglect. Prior literature demonstrates good test-retest reliability and internal consistency across a range of samples (58).

### Interventions

2.6

The first session for both the ReACT and supportive therapy intervention arms will be conducted in-person at UAB and last 1.5 hours. This visit will be followed by 11 one-hour telehealth sessions, resulting in an overall equivalent intervention dose across intervention arms. The first therapy session will be held approximately one week after the baseline visit. Subsequent sessions will typically be scheduled weekly such that the participant will complete the intervention in 3 months. However, should therapy sessions not occur weekly due to illness, holidays, vacation, etc., the duration of time between the first and final sessions will be limited to five months.

Participants will be offered the treatment to which they were not randomized after the 2-month follow-up when the study is completed. Study investigators and staff will not provide any medication-related advice to participants. Both supportive therapy and ReACT interventionists will be master’s level therapists. All interventionists will receive extensive training by the PI and last author (AF) on their respective intervention, participate in weekly supervision, and complete yearly training sessions.

#### Retraining and control therapy

2.6.1

The protocol for ReACT has been described in previous publications (4, 59). In short, for participants randomized to ReACT, the first session will include: 1) an etiological explanation of FND, 2) an individualized plan for retraining FND symptoms, 3) a family and friend plan for responding to FND symptoms, and 4) a plan to return to school and activities. Therapists will conduct this and all subsequent sessions using the ReACT Precision Treatment Tool, an adaptive digital manual that tailors session content to the issues most relevant to each patient at that time. Guided by this tool, subsequent sessions will focus on modifying and adapting the patient’s individualized plan based on patient progress and needs, addressing symptom triggers and avoidance behaviors, generalizing CBT skills to manage stressors or mood concerns, and developing a relapse prevention plan. Each session will include both individual and joint discussions with the participant and parent/guardian.

#### Supportive therapy

2.6.2

Supportive therapy is an unstructured therapy based on the assumption that relief from problems can be achieved by discussion with a therapist (60). The purpose of supportive therapy is not to acquire new skills or find solutions to problems. The etiological model provided to patients will focus on FS as the result of stress or mood. Supportive therapy sessions will focus on discussion of stressors or mood concerns and how they are related to their FS, and therapists will provide empathy. Patients will be asked about things that help them deal with stressors, but consistent with supportive therapy protocols, specific strategies will not be generated by the therapist (60). Each session will be the same duration as ReACT sessions and follow the same structure as the ReACT intervention (i.e., individual and joint discussions with the participant and parent/guardian) to further ensure dose equivalence with ReACT.

To minimize expectancy bias, both ReACT and supportive therapy will be described to families as credible interventions that may help manage FS and improve coping. Participant-related treatment expectancy will be assessed at the first therapy session using the Credibility/Expectancy Questionnaire (described in section 2.5.5).

#### Treatment fidelity

2.6.3

All ReACT and supportive therapy sessions will be videotaped, and trained research assistants will review and score 20% of the sessions using standards of published guidelines (61, 62) to ensure treatment fidelity and no contamination between behavioral interventions. Separate fidelity checklists for ReACT and supportive therapy will be used to ensure each treatment is delivered as intended, with items rated for both presence and quality. Fidelity will be calculated as the percentage of total possible points earned, based on the sum of item scores divided by the checklist’s total point value. For each therapist’s first 5 participants, two research assistants will score the same sessions until the scoring is above 95% agreement to ensure validity of fidelity ratings. Adequate fidelity will be defined as scoring above 80% threshold. If fidelity is insufficient for any of the therapists’ first patients, additional training will be provided until fidelity is reached. Fidelity will be re-assessed at 3- and 6-months after enrollment begins and before final analyses.

#### Participant retention

2.6.4

All efforts will be taken to ensure enrolled and randomized participants are followed for the entire study period. To facilitate this, participants will be asked to provide their contact number and email address, their parent/guardian’s contact number and email address, and an additional contact number who can be reached out to in the event the participant or parent/guardian cannot be reached. Further, reminder calls will be made the day before all appointments and follow-up visits will be scheduled over Zoom prior to therapy appointments. Follow-up appointments will also be offered at flexible times with weekend and before and after school availability.

Using an intent-to-treat analysis, participants who choose to withdraw from the treatment but wish to complete remaining study visits will complete a lab visit 7 days after withdrawing and 2-months later. Participants who do not ask to withdraw from the study or treatment, but no-show their therapy session or lab visit, will be called the day of their appointment. If they cannot be reached, a voicemail will be left including call back information. If the participant does not respond within three days, another call will be made. If after one week there has been no communication from the participant, a final call will be made to the participant, parent/guardian, and additional contact. The participant will be considered lost to follow-up if no response is provided after this point.

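### One call sequence for missed therapy sessions and missed lab visits can class a silent participant as lost to follow-up weeks to months before any primary outcome is due

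*Protocol article*

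**What the plan says.** Section 2.6.4 (Participant retention) opens with the aim: "All efforts will be taken to ensure enrolled and randomized participants are followed for the entire study period". Email addresses and telephone numbers are collected for the participant and the parent/guardian, plus a number for one additional contact.

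Two groups are then treated differently.

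- **Open withdrawal from treatment.** Under an intent-to-treat heading, "participants who choose to withdraw from the treatment but wish to complete remaining study visits will complete a lab visit 7 days after withdrawing". A second visit is planned two months after that.
- **Silent non-attendance.** The sequence starts on the date of the missed appointment: "Participants who do not ask to withdraw from the study or treatment, but no-show their therapy session or lab visit, will be called the day". A voicemail is left if nobody answers. Next: "If the participant does not respond within three days, another call will be made". Then: "If after one week there has been no communication from the participant, a final call will be made to the participant, parent/guardian, and additional contact". Finally: "The participant will be considered lost to follow-up if no response is provided after this point".

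The second sequence is the same whether the missed appointment was a therapy session or an outcome visit. It uses telephone only, and no waiting time after the final call is given.

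Section 2.4 and Table 1 place every primary outcome at baseline, one week after treatment and two months after treatment, with none during therapy. Section 2.6 plans 12 sessions, typically weekly, and allows the course to stretch to a five-month maximum: "should therapy sessions not occur weekly due to illness, holidays, vacation, etc., the duration of time between the first and final sessions will be limited". Section 2.7 plans multiple imputation where appropriate, and Section 2.7.1 recruits 80 to allow for 20% dropout.

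**The concern.** Stopping therapy and being lost to outcome assessment are different events, and a trial that analyses by intention to treat needs to keep them apart. Here one rule covers both. A family that misses a mid-course session and cannot be reached is given a study-level status, although the visits that matter for the primary analysis are not yet due.

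A participant closed out during therapy has no post-baseline primary outcome at all. Imputation would then rest on baseline values and whatever weekly diaries and questionnaires had been collected. Disengagement may also differ by arm: Section 2.6.2 describes supportive therapy as not intended to teach skills or solve problems, and families may react to that. The documents do not show such a difference, but if it arose, imputation that assumes data missing at random would not fully repair it.

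**Working it through.** **1. The plan's own figure.** The only stated number that depends on loss is the recruitment target: 64 / (1 − 0.20) = 80. This reproduces. The margin is 80 − 64 = 16 participants, and each one is 1/80 = 1.25% of the sample.

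**2. Inputs for the timeline.**
- 12 sessions, weekly (Section 2.6): session k falls on day 7 × (k − 1), so session 12 is on day 77.
- Outcome visits one week and two months after treatment (Section 2.3). With a month taken as 30.4 days, two months is about 61 days. The visits are on day 77 + 7 = 84 and day 77 + 61 = 138.
- Final call one week after the no-show (Section 2.6.4). The wait after that call is not stated and is taken as zero.
- Longest allowed course: five months, about 152 days. Sessions are assumed evenly spaced at 152 / 11 = 13.8 days, with visits on days 159 and 213.

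**3. Formula.** Day lost = day of missed session + 7. Lead time = visit day − day lost.

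| Schedule | Missed session | Day missed | Day lost | Days before 1-week visit | Days before 2-month visit |
|---|---|---|---|---|---|
| Weekly | 2 | 7 | 14 | 70 | 124 |
| Weekly | 4 | 21 | 28 | 56 | 110 |
| Weekly | 6 | 35 | 42 | 42 | 96 |
| Weekly | 12 | 77 | 84 | 0 | 54 |
| Five months | 2 | 14 | 21 | 138 | 192 |
| Five months | 6 | 69 | 76 | 83 | 137 |

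For session 4 on the weekly schedule, 56 / 7 = 8 weeks and 110 / 7 = 15.7, about 16 weeks.

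**4. Sensitivity to the unstated wait.** Any wait after the final call shortens each lead time by the same number of days. With a further week, the session 4 figures become 49 and 103 days. The conclusion does not depend on this assumption, except for a no-show near the end of therapy.

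**5. The two groups side by side.** Someone who openly stops treatment around session 4 and agrees to visits is offered one 7 days later and another two months after that. Someone who goes silent at the same session, without declining anything, reaches the final call at the same 7 days, and no route to either visit is described.

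**6. What cannot be computed.** The article gives no rate of silent no-shows, so the number of outcomes at risk is unknown. For illustration only, total loss of 25% or 30% would leave 80 × 0.75 = 60 or 80 × 0.70 = 56 completers, against the 64 planned for.

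**The case against.** The strongest reply is that the rule is neither as quick nor as final as it may look. A single unanswered call is not enough: three rounds must fail, the last including the parent/guardian and a third party. Nothing in the article cancels later visits, bars renewed contact or excludes someone who reappears. Section 2.6.4 also promises a reminder call before every appointment. An article may leave re-contact procedures to the full protocol. People who withdraw openly keep visits only because they have been reached and have agreed. All of this is fair. What remains is that the article does state an operating rule, with a final call followed by a study-level status, and does not separate therapy from outcome visits. Site staff following it would have reason to stop.

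A reader might infer three stronger things, and the documents do not support them.

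- **That the rule breaches intent-to-treat.** It removes nobody from the analysis set, and Section 2.7 plans imputation and sensitivity analyses. The effect is missing outcomes.
- **That it contradicts the session gaps allowed in Section 2.6.** A five-month course averages about two weeks between sessions, but an interval between sessions is not a silence. A family that reschedules or answers any call never meets the rule. The two sections are in tension and no more.
- **That it cuts short safety follow-up.** No participant-level safety follow-up period is stated. The suicide-risk scale is scheduled at both outcome visits and would be missed with them, but that is an inference about the visits, not a stated safety provision that is lost.

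**Conclusion.** The point holds as a design weakness that should be corrected. As written, a silent no-show during therapy can be classed as lost to follow-up well before any post-baseline primary outcome is due. For session 4 on a weekly schedule the lead is about 8 and 16 weeks. Across sessions 2 to 12 on that schedule it runs from 70 down to 0 days before the 1-week visit, and from 124 down to 54 days before the 2-month visit. It is longer if the course is stretched.

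This rests on the ordinary reading that a final call followed by that status ends active contact, on evenly spaced sessions, and on no wait after the final call. The harm is avoidable missing primary data, possibly uneven between arms, drawn from a margin of 16 participants. Its frequency is unknown. If the full protocol already provides for re-contact at the outcome visits, one clarifying sentence settles the matter.

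**What to change.** Rewrite the last part of Section 2.6.4 so that:

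1. the one-week call sequence decides only the status of the missed appointment, or of treatment (session missed, treatment discontinued);
2. every randomized participant stays in outcome follow-up unless they withdraw from the study;
3. contact is attempted again when the 1-week and 2-month visits fall due, using the email addresses already collected and the additional contact as well as the telephone, with a statement of the date from which those visits are counted when therapy was not completed;
4. loss to follow-up is assigned only when the 2-month visit has passed without contact.

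Section 2.6 should be cross-referenced, so that staff can tell a rescheduled session from a no-show. The cost is one revised paragraph and a few extra calls or emails per silent family, some of whom will never answer.

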#### Power and sample size

2.7.1

A Cohen’s d estimate of effect size of 0.5 was determined based on effect sizes from previously published studies using the Magic and Turbulence Task (26, 63, 64) and assessing change in pain sensitivity, pain tolerance, and cortisol for the CPT (33, 65, 66). A power analysis determined a sample size of N = 64 will be required to obtain >80% power at the two-tailed 0.05 alpha level to detect differences in the ReACT and supportive therapy interventions. However, 80 participants will be recruited to account for a 20% dropout rate.

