### Study design

2.1

The study is a single site two-arm parallel randomized controlled trial for adolescents with FS. Participants will undergo 12 sessions of either ReACT or supportive therapy. The study will be conducted at the University of Alabama at Birmingham (UAB) and will include 80 participants with FS and their family member enrolled from March 2024 to December 2026. The study was approved by the Institutional Review Board (IRB) at UAB and is registered at ClinicalTrials.gov under registration number #NCT06007053.

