## Strengths, limitations, and additional considerations

4

The present study has several notable strengths, including a focus on identifying mechanistic treatment targets for pediatric FS beyond mood and trauma-related factors, with direct relevance to FS frequency and clinical outcomes. Further, the integration of objective biomarkers as measures of treatment response and provider-centered tools to support fidelity and dissemination represent an important step toward optimizing and scaling evidence-based interventions for pediatric FS. At the same time, several limitations and broader considerations warrant note. First, although the Magic and Turbulence Task has been shown to be sensitive to change in pediatric FS and other conditions, formal evaluation of test-retest reliability and practice effects has not yet been established.

Second, although the CPT is a well-established measure for assessing pain catastrophizing and perceived pain, the present study does not capture responses to other physiological sensations (e.g., increased heart rate) or cognitive-affective responses (e.g., catastrophizing) in everyday contexts. Future studies will benefit from incorporating multiple complementary tasks to more comprehensively assess catastrophic symptom expectations across domains. Finally, although the present design intentionally focused on pediatric FND, the biobehavioral processes examined may have implications for understanding and informing intervention approaches in adult FND, representing an important avenue for future translational research.

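### The stated 64 is the number per arm for d = 0.5; used as the trial total it gives about 50% power unadjusted, not more than 80%

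*Protocol article*

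**What the plan says.** All the inputs are in section 2.7.1 (Power and sample size) of the protocol article. For the effect size, a Cohen's d "estimate of effect size of 0.5 was determined based on effect sizes from previously published studies". For the sample size, "A power analysis determined a sample size of N = 64 will be required to obtain >80% power at the two-tailed 0.05 alpha level", the target being a difference between ReACT and supportive therapy. For attrition, "80 participants will be recruited to account for a 20% dropout rate".

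Section 2.1 (Study design) describes a two-arm parallel trial that "will include 80 participants with FS and their family member enrolled from March 2024 to December 2026". So 80 is the whole trial, and 64 is the whole-trial number left after dropout.

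Section 2.7 (Data analysis plan) makes the primary comparison a between-group one, with a separate ANCOVA for each outcome adjusted for its pre-treatment value. Section 2.7.1 mentions neither a baseline-to-follow-up correlation nor any variance reduction from that adjustment. On the Magic and Turbulence Task, section 4 says that "formal evaluation of test-retest reliability and practice effects has not yet been established".

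**The concern.** For d = 0.5, two-sided 5% alpha and 80% power, 64 is the familiar sample size per group for a two-sample t test. The protocol uses the same number as the sum of two groups, so each arm would have half of what the calculation calls for.

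This is the only power statement for the primary outcomes. If it is wrong, a trial presented as adequately powered has about an even chance, before any covariate gain, of missing the effect it was designed to find. Section 3 presents the results as the basis for establishing the treatment targets and for planning a larger trial. A non-significant result from a trial believed to have more than 80% power could be read as evidence that ReACT does not engage its targets.

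**Working it through.** **Inputs.** From section 2.7.1: d = 0.5, two-sided alpha 0.05, power above 80%, N = 64, dropout 20%. From section 2.1: two parallel arms, 80 in total. The allocation ratio is not stated; 1:1 is assumed, which is the most favourable case for power.

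**1. Reproduce the stated figure.** The normal approximation per arm is n = 2(z₀.₉₇₅ + z₀.₈₀)²/d² = 2(1.960 + 0.842)²/0.25 = 62.8, so 63. The t-test solution is 63.77, so 64. Power by the noncentral t is 79.5% at 63 per arm and 80.1% at 64 per arm. The stated 64 with power just above 80% therefore reproduces exactly as a **per-arm** number.

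**2. Check which 64 the protocol uses.** 64/(1 − 0.20) = 80, and 80 is the total for both arms. The dropout step is arithmetically right, but it is applied to a total of 64, that is 32 per arm.

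**3. Power with 32 per arm.** The noncentrality is d√(n/2) = 0.5 × √16 = 2.00. The two-sided critical value of t on 62 degrees of freedom is also about 2.00, so power must be close to one half.

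| Evaluable | Power at d = 0.5 |
|---|---|
| 32 per arm (64 total) | 50.4% |
| 40 per arm (80 total, no dropout) | 59.8% |
| 64 per arm (128 total) | 80.1% |

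The effect detectable with 80% power at 32 per arm is d = 0.71.

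**4. Allow for the planned ANCOVA.** If d is on the unadjusted scale, adjusting for a baseline value with correlation r divides the residual SD by 1/√(1 − r²). The noncentrality becomes 2.00/√(1 − r²), on 64 − 3 = 61 degrees of freedom. No r is stated, so a range is shown.

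| Assumed r | Power at N = 64 total | Total evaluable for 80% | Recruited (÷ 0.8) |
|---|---|---|---|
| 0 | 50% | 128 | 160 |
| 0.3 | 54% | 118 | 148 |
| 0.5 | 62% | 98 | 123 |
| 0.6 | 69% | – | – |
| 0.7 | 79% | 68 | 85 |

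Power reaches 80% at N = 64 when r is about 0.71. At r = 0.5 the detectable effect is about 0.71 × √0.75 = 0.62. If d is already on the covariate-adjusted scale there is no further gain and power stays at about 50%.

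**5. Try other routes to a total of 64.** A one-sided 5% test would still need 51 per arm and has 63% power at 32 per arm; the article says two-tailed. A paired test would need only 34 people, and at 64 has about 98% power; it does not produce 64 and is not the between-group comparison planned. Neither explains the stated number.

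**The case against.** The strongest objection is that the 50% figure belongs to an unadjusted t test, whereas section 2.7 plans ANCOVA. Power under the planned model is higher whenever the baseline value is predictive, and with r of about 0.71 or more the stated claim would be true. A journal article condenses the full power section, so a correlation may have been assumed without being printed. The article also names no test, and it says that part of the evidence for d came from studies of change in the cold pressor measures; a d on a change scale would alter the calculation. That a per-arm number was used as a total is therefore an inference.

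Some of this stands. Power should be given as a range over r, not only as 50%, and 128 is the requirement only without covariate gain. The section 4 caveat means that reliability of the Magic and Turbulence Task is unknown, not that it is low, and it says nothing about cortisol, pain tolerance or pain catastrophizing.

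The discrepancy itself is not removed. This is not a complaint about missing detail: effect size, alpha, power and N are all printed, and they do not agree for the stated comparison. They agree exactly if 64 is per arm. Reaching 80% with 64 in total would need a correlation of about 0.71 for every primary outcome, since each has its own ANCOVA, and nothing in the article supports that. The article does defer a fully powered trial, but for seizure-frequency efficacy; that does not withdraw the claim of more than 80% for the treatment targets, which are the primary outcomes.

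**Conclusion.** The power statement is wrong as written. On the printed inputs, more than 80% power at d = 0.5 needs 64 per arm. The trial plans for 64 evaluable in total and has 50.4% power without covariate gain. Under the planned ANCOVA, power runs from about 54% to 79% for correlations from 0.3 to 0.7. The detectable effect at 80% power is d = 0.71 unadjusted, or 0.62 at r = 0.5.

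These figures assume 1:1 allocation, d on the unadjusted outcome scale for the ANCOVA range, and the stated 20% dropout. Unequal allocation, or any multiplicity adjustment across the several primary outcomes, would lower power further. A stated and justified correlation of at least 0.71 for each primary outcome would restore the claim.

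**What to change.** Rewrite section 2.7.1 in one of two ways.

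- **Keep the sample size and correct the claim.** State that 64 evaluable participants (32 per arm) give about 50% power for d = 0.5 without covariate gain and about 62% at an assumed baseline correlation of 0.5, with detectable effects at 80% power of d = 0.71 and 0.62 respectively. Give the range over plausible correlations, since no value is established for the sense-of-control task. If the 80% target is mentioned, state the total it needs together with the assumption: 128 evaluable (160 recruited) with no covariate gain, 98 evaluable (123 recruited) at r = 0.5.
- **Keep the claim and support it.** Name the test, the scale of d and the assumed correlation, and justify a value of at least 0.71 for each primary outcome.

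Under the first option it would also help to say that a non-significant result will not be taken as evidence that the targets are not engaged, and to report the between-arm differences with 95% confidence intervals. The expected half-width without adjustment is about 2.00 × √(2/32) = 0.50 SD.

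The first option changes wording only: no more patients, visits or changes to the analysis. Its cost is a less favourable stated power.
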